### 2.2 Secondary Goals

The secondary objectives of the study are to evaluate:

- Patient Reported Quality of life [timeframe: 7 days after radiation treatment end date]
- Response rate [timeframe: at 3 months (+/- 14 days) post radiation treatment start date]
- Local control rate [timeframe: up to 24 months after the completion of radiation treatment]
- Relapse-free survival [timeframe: up to 24 months after completion of radiation treatment]

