7.2.3 Outcomes

- Adverse events (CTCAE version 5.0) will be assessed at Baseline, End of Treatment, Day 7 post-RT, Day 14 post-RT, and at 3 months within the windows defined in **Section 4.0**. The primary outcome is acute toxicity, defined as any adverse event grade 2 or higher at least possibly related to radiation treatment that occurs up to 14 days after the end of radiation treatment.
- Patient reported outcomes (FACIT-Fatigue scale) will be collected at Baseline, End of Treatment, Day 7 post-RT and 3 months post-RT within the windows defined in **Section 4.0**.
- Financial toxicity, determined by the COST-FACIT QOL, will be evaluated after RT at the end of treatment (+/- 1 day).
- Financial health care expenditure (see **Section 7.2.8**) will be collected after RT at the end of treatment.
- Response rate will be obtained during follow-up imaging and clinical exam at 3 months (+/- 14 days) post radiation treatment.
- Local recurrence rate will be obtained during follow-up imaging and clinical exam at 3 months, 6 months, 12 months, 18 months, and 24 months post radiation treatment within the windows defined in **Section 4.0**.
- Overall survival will be assessed during follow-up at 3 months, 6 months, 12 months, 18 months, and 24 months post radiation treatment per clinician's discretion within the windows defined in **Section 4.0**.

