7.2.5 Quality of Life

Patient Reported Outcomes will be collected at Baseline, End of Treatment, Day 7 post-RT, and 3 months post-RT completion date and will be based on the FACIT-Fatigue questionnaire within the windows defined in **Section 4.0**.

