### 16.3 Secondary

The following definitions are used for the secondary endpoints of interest:

• Response rate at 3 months post radiation treatment: is reported as a proportion calculated as the number of cases with complete response (CR) or a partial response (PR) at 3-month post radiation imaging based on Lugano criteria divided by the total number of treated patients. Treated patients who do not have a 3-month evaluation will be classified as a non-response.

• Local control rate at 2-years: defined from the time of registration to local relapse that overlaps the treated site (95% isodose line).

• Patient Reported Outcomes/Quality of life: FACIT-Fatigue given as SOC for Lymphoma patients within 3 months after end of radiation treatment will be used as outlined in section 4.0 and 7.0.

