16.6.2.4 Quality of life: FACIT-Fatigue scores along with validated subscales given as SOC for Lymphoma patients will be collected from baseline to up to 3 months after radiation treatment. The FACIT Fatigue consists of 13 Likert-scale items scored 0 (not at all) to 4 (very much). We will calculate the fatigue subscale score at each assessment by first reverse scoring the following items: HI7, HI12, An1, An2, An3, An4, An8, An12, An14, An15, An16 by subtracting the response from 4 and then sum the 13 items to obtain a score. Then multiple the sum of the items by the number of items in the subscale (13), then divide by the number of items the patient answered. The Fatigue Subscale score ranges from 0 to 52 where a higher score indicates a better quality of life. We will estimate the difference between treatment arms in the trajectory (slope) of the Fatigue Subscale score including all available scores from end of treatment to 3 months post RT in a longitudinal mixed effects regression model with a random effect for patient. Fixed effects will include an indicator variable for treatment arm (1=9 Gy, 0=24 Gy), time defined as the number of weeks (7 days) from end of treatment to FACIT-Fatigue assessment (continuous), and an interaction term for treatment arm and time. The estimates from the interaction term along with 95% confidence interval (profile likelihood) will be interpreted as the difference in trajectories between treatment arms. A likelihood ratio test will be used to compare treatment arms on the difference in trajectories of fatigue subscale score.

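### The only fatigue test compares recovery slopes from end of RT to 3 months, which answers neither stated quality-of-life timeframe and turns an early benefit that fades into a negative interaction

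*Protocol*

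**What the plan says.** The protocol gives the timeframe for this endpoint twice, differently. Section 2.2 lists "Patient Reported Quality of life [timeframe: 7 days after radiation treatment end date". Section 16.3 states that "FACIT-Fatigue given as SOC for Lymphoma patients within 3 months after end of radiation treatment will be used".

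On data collection, section 7.2.3 says "Patient reported outcomes (FACIT-Fatigue scale) will be collected at Baseline, End of Treatment, Day 7 post-RT and 3 months post-RT", and sections 4.0 and 7.2.5 agree. A baseline and three later scores are therefore scheduled.

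Section 16.6.2.4 fixes the analysis:
- The outcome is the Fatigue Subscale score (0 to 52, higher meaning less fatigue), modelled "including all available scores from end of treatment to 3 months post RT in a longitudinal mixed effects regression model". Each patient gets a random effect.
- The fixed part holds arm (coded 1 for 9 Gy), continuous weeks counted from the last day of radiation, and the product of the two. The product is the quantity to be interpreted, and its 95% interval is by profile likelihood.
- For inference, the section states: "A likelihood ratio test will be used to compare treatment arms on the difference in trajectories of fatigue subscale score".

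Baseline enters neither as an outcome nor as a covariate. No contrast at Day 7 or at any other visit is specified.

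**The concern.** The stated objective concerns how fatigued patients are 7 days after radiation or, on the section 16.3 wording, over the following 3 months. The planned test concerns how fast scores change once radiation has ended. These can differ in sign. If radiation fatigue is transient, the arm with more of it at the end of treatment has further to recover and shows the steeper slope.

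The trial's hypothesis is less acute toxicity with the reduced dose. An early difference that closes by 3 months is therefore a natural pattern to expect, and it is one for which the tested coefficient points away from the benefit. Without a baseline term, the model also cannot separate faster recovery from greater initial loss. The matter is not left open for a later plan, because the protocol itself names the model, the coding, the interval and the test.

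**Working it through.** The protocol states no mean, SD, effect size or power for fatigue, so it has no figure to reproduce.

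**Inputs from the protocol.** Visits are at end of treatment, Day 7 and 3 months (sections 4.0 and 7.2.5), taken as t = 0, 1 and 13 weeks. Arm is coded 1 for 9 Gy and higher scores are better (16.6.2.4). There are 51 patients per arm (16.5.4).

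**Assumptions.** Complete data, within-patient SD of 5 or 6, two-sided 5% level, and the mean differences shown below.

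**Weight of each visit.** With complete data at common times, the interaction from a random-intercept model equals the between-arm difference in least-squares slopes. Each visit has weight (t − mean t)/Σ(t − mean t)².
- Mean t = 14/3 = 4.667, so the deviations are −4.667, −3.667 and 8.333.
- Sum of squares = 21.78 + 13.44 + 69.44 = 104.67 (from unrounded deviations).
- Weights = −0.0446, −0.0350 and +0.0796, which sum to zero.

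With Day 7 moved between days 5 and 9 and the 3-month visit between weeks 11 and 15, the Day 7 weight stays negative, from −0.030 to −0.042.

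**Direction.** Let d0, d1 and d13 be the reduced-dose minus 24 Gy differences. The interaction is −0.0446·d0 − 0.0350·d1 + 0.0796·d13.
- Constant +5/+5/+5: 0.00 points per week.
- Early +5/+5/0: −0.40.
- Day 7 only, 0/+5/0: −0.18.
- Early harm −5/−5/0: +0.40.

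**Size.** The standard error of the interaction is √(2s²/(51 × 104.67)), which is 0.0968 for s = 5 and 0.1161 for s = 6. The between-patient SD cancels. The chance of a significantly lower slope for the reduced-dose arm is Φ(|interaction|/SE − 1.96):

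| Assumed difference (end of RT / Day 7 / 3 months) | Interaction per week | s = 5 | s = 6 |
|---|---|---|---|
| 4 / 3.5 / 0 | −0.301 | 87% | 74% |
| 2 / 1.75 / 0 | −0.150 | 34% | 25% |
| 4 / 3.5 / 2 | −0.142 | 31% | 23% |
| 0 / 3.5 / 0 | −0.123 | 24% | 18% |
| 4 / 3.5 / 3.5 | −0.022 | 4% | 4% |

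Simulated trials for the first row gave 72% to 87%, with no trial significant in the other direction. A separate simulation fitted the mixed model with its likelihood ratio test (+5/+5/0, SDs 8 and 6, 150 runs). It gave 95% significantly negative and 0% positive. With a constant +5 it rejected in about 5%, the null rate.

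**What the arm term carries.** For 4/3.5/0 the mean difference is 2.5. The fitted difference at end of treatment is 2.5 + 0.301 × 4.667 = 3.90, and at Day 7 it is 3.90 − 0.30 = 3.60, close to the true 3.5. For 0/3.5/0 the fitted Day 7 difference is 1.167 + 0.1226 × (4.667 − 1) = 1.62, less than half of 3.5, because a straight line cannot follow that shape.

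**What baseline adds.** Take a between-patient SD of 8 and a within-patient SD of 5. The total SD is √89 = 9.43 and the correlation with baseline is 64/89 = 0.72. For a Day 7 comparison the SE is 9.43 × √(2/51) = 1.87 unadjusted, and 1.87 × √(1 − 0.72²) = 1.30 adjusted. For a 3.5-point difference, simulated power is about 47% unadjusted and 77% adjusted.

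**The case against.** Several stronger readings are tempting, and the protocol does not support them.

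- *The plan would declare the reduced dose worse.* A reader might infer this, but section 16.6.2.4 only calls the interaction a difference in trajectories. The test is two-sided and no rule says that a flatter slope is unfavourable. A careful reader who sees a higher starting level with a flatter slope can recognise less early fatigue.
- *The model cannot show the benefit.* This goes too far. The arm coefficient is the fitted difference at end of treatment, and adding one week of interaction gives a fitted Day 7 difference. What stands is that neither is named for testing or reporting, and both depend on a straight line over 13 weeks.
- *Day 7 is the only stated time.* It is not. Section 16.3 says within 3 months, and the modelled window matches that. This does not rescue the test, since a benefit held constant over the whole 3 months also gives zero.
- *Omitting baseline biases the comparison.* A randomised comparison at a visit is unbiased without it. The loss is precision and, for the slope, interpretation.
- *A misleading result is to be expected in 87% of trials.* That figure needs a 4/3.5-point benefit that disappears completely and a within-patient SD of 5.

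It is also fair that a recovery slope is a legitimate descriptive question, and that this is a secondary endpoint. Section 16.5.1.1 rests the decision on further study on acute toxicity and 2-year local control only.

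**Conclusion.** The point holds as a mismatch between objective and test. No contrast in section 16.6.2.4 corresponds to the Day 7 objective in section 2.2, and the slope test does not answer the 3-month wording in section 16.3 either. A constant benefit is missed, and a fading one gives a negative interaction. That follows from the visit times and the coding, whatever the means and SDs.

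The size is uncertain because it rests on assumed values. A significantly lower slope for the less fatigued arm ranges from about 4% of trials to 87%, and is 23% to 34% when the benefit is halved or partly persists. The primary analysis, the sample size and the decision rule are unaffected. It should be corrected before the fatigue data are analysed, but it does not threaten the trial's main conclusion.

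**What to change.** 1. Reconcile the quality-of-life timeframe in sections 2.2 and 16.3, naming Day 7 as the time of the tested comparison.
2. In section 16.6.2.4, make the tested contrast the baseline-adjusted mean difference in FACIT-Fatigue at Day 7. Estimate it from a repeated-measures model with visit as a category (end of treatment, Day 7, 3 months), arm, arm by visit, and baseline score as a covariate.
3. Report the end-of-treatment and 3-month differences with 95% confidence intervals from the same model.
4. Keep the slope interaction as a description of recovery only.

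The cost is one rewritten paragraph and the alignment of two timeframe statements. All the scores are already scheduled, so no visit, questionnaire or patient is added.

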16.6.2.5 Exploratory Analyses

Financial toxicity: COST-FACIT with added questions to assess specifically for travel and accommodation expenses, travel distance and time, and loss of work time for patient and care givers scores will be assessed at end of treatment and described separately for the two groups. The financial toxicity score will be calculated using items FT1-FT11 where items FT2, FT3, FT4, FT5, FT8, FT9, and FT10 will first need to be reverse scored by subtracting the response from 4 and then sum the individual items to obtain a score. Then multiply the sum of the item scores by the number of items in the scale (11) and divide by the number of items the patient answered. The financial toxicity score ranges from 0-44 where a higher score indicated better financial well-being. The financial toxicity score will be summarized separately for the two treatment groups with the mean, standard deviation, median, 25^th^ percentile, and 75^th^ percentile. No comparison between treatment groups will be conducted. Individual items will be described with mean, standard deviation.

Financial health care expenditure will be determined by first obtaining base cost rates from Mayo Clinic’s reimbursement database for all codes included in the planning, treatment, and management of patient’s enrolled in both arms. Mean total radiotherapy costs will then be calculated using inflation adjusted standardized Medicare rates and summarized separately for the 2 treatment arms; a linear regression model will be used to estimate the difference in Financial health care expenditure between the two treatment arms.

Biopsies of enrolled patients will be evaluated for pathological assessment of cellular and genetic mutations. This includes: TP53 alteration by FISH and expression of TP53, MYC and proliferation index (Ki-67) by immunohistochemistry stain (IHC).

Baseline PET/CT scan of patients will be sent to MIMvista to undergo autosegmentation to calculate the MTV, TLG and SUVmax of their disease.

Multivariable models will be used to evaluate associations of these biomarkers separately with local control (logistic regression) and response (Cox proportional hazards). Models will include biomarker, treatment arm as a covariate along with potentially confounding variables.

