### This leaves us with important unanswered questions. 1) Can we find a more optimal intermediate dose between 4 Gy and 24 Gy that is similarly effective with respect to disease control as 24 Gy but has shorter treatment course, lower clinical and financial toxicity, and less financial health care expenditure? 2) Can we personalize RT for patients with indolent NHL by identifying prognostic predictors of local control and radio-resistance?

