2.3 Exploratory Goals

- Financial toxicity will be assessed at the end of radiation treatment.
- Financial Health Care Expenditure will be assessed at the end of radiation treatment
- Late Toxicity. Late adverse events will be assessed at 3 months post radiation treatment. Toxicity refers to those adverse events that are possibly related to radiation treatment.

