## **4.0 Test Schedule**

|  |  | **Active Monitoring Phase** | | | **Clinical Follow-Up** | | |
| --- | --- | --- | --- | --- | --- | --- | --- |
| **Tests and procedures** | ***≤ 45 days prior to registration*** | ***End of Treatment*** | ***Day 7***  ***post-ISRT*** | ***Day 14***  ***post-ISRT*** | ***3 Months***  ***post-RT^1^*** | ***6 Months***  ***post-RT*** | ***Every clinically indicated follow-up***  ***(q 6 months)^1^*** |
| Window |  | ±1 day | ±2 days | ±2 days | ±14 days | ±30 days | ±30 days |
| History and exam, PS^2^ | X |  |  |  | X | X | X |
| Radiation Oncology consult^2^ | X |  |  |  |  |  |  |
| Adverse Event assessment^3^ | X | X | X | X | X |  |  |
| Pregnancy test^2,^4 | X |  |  |  |  |  |  |
| Hematology group: CBC with 5-part differential  (HgB, WBC, PLT, LDH)^2^ | X |  |  |  |  |  |  |
| PET/CT ^2^ | X  (90 days) |  |  |  | X  (strongly consider, unless FDG negative at baseline) | X* | X* |
| CT Chest/Abdomen/Pelvis +/- Neck^2, 7^ |  |  |  |  | X  (if PET not done) | X* | X* |
| Endoscopy with gastric biopsy (only if gastric lymphoma)^2^ | X  (***≤*** 90 days) |  |  |  | X^6^ | X** |  |
| Patient Reported Outcomes (Appendix II: FACIT-Fatigue)^3^ | X | X | X |  | X |  |  |
| Financial Toxicity Questionnaire  (Appendix II: COST-FACIT)^3^ |  | X |  |  |  |  |  |
| Optional Research,  tissue specimen5^,R^ |  | X |  |  |  |  |  |

Radiation treatment (RT) = 3 vs. 12 fractions (5 days vs. 16 days ±2 days)

^1^ Follow-up assessments will be completed as per clinician’s discretion.

^2^ Standard of care

^3^ Research non-billable

^4^ For persons of childbearing potential only. Must be done ≤7 days prior to registration.

^5^ Historic tissue specimen may be pulled and used for analysis by end of study.

^6^ +/- 30 days

^7^ CT and/or PET should not be mandated for patients with primary cutaneous lymphoma where physical exam is used for evaluation of treatment response..

^R^ Research funded

* CT chest/abdomen/pelvis +/- neck or PET/CT or PET/MRI ok at these time points

** If 3 month biopsy was positive

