7.2.6 Financial toxicity

Financial toxicity will be determined using a questionnaire completed by the patient at the end of their ISRT (fraction 3 for experimental arm and fraction 12 for the SOC arm). This questionnaire will entail the validated FACIT-COST scale with added questions to assess specifically for travel and accommodation expenses, travel distance and time, and loss of work time for patient and care givers.

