16.4.1.1 TP53 gene alteration by Fluorescence in situ hybridization (FISH)

16.4.1.2 Expression of TP53, MYC and proliferation index (Ki-67) by immunohistochemistry stain (IHC)

16.4.2 Baseline PET/CT scan of patients will be sent to MIMvista to undergo autosegmentation to calculate the MTV, TLG and SUVmax of their disease to correlate it with disease local relapse and treatment response.

16.4.3 Financial toxicity: financial side effects induced by cancer treatment that will be assessed by a modified COST-FACIT questionnaire as outlined in section 4.0 and 7.0.

16.4.4 Financial health care expenditure reflects the costs spent on health care and related activities attributable to this cancer treatment and will be assessed as outlined in section 4.0 and 7.0.

16.4.5 Sensitivity analysis to assess differences in the different radiation dose regimens in the experimental treatment arm.

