# Appendix II: Patient Questionnaires

COST – FACIT (Version 2)

Below is a list of statements that other people with your illness have said are important**. Please circle or mark one number per line to indicate your response as it applies to the past 7 days.**

|  |  | **Not at all** | **A little bit** | **Some-what** | **Quite**  **a bit** | **Very much** |
| --- | --- | --- | --- | --- | --- | --- |
|  |  |  |  |  |  |  |
| FT1 | I know that I have enough money in savings, retirement, or assets to cover the costs of my treatment | 0 | 1 | 2 | 3 | 4 |
| FT2 | My out-of-pocket medical expenses are more than I thought they would be | 0 | 1 | 2 | 3 | 4 |
| FT3 | I worry about the financial problems I will have in the future as a result of my illness or treatment | 0 | 1 | 2 | 3 | 4 |
| FT4 | I feel I have no choice about the amount of money I spend on care | 0 | 1 | 2 | 3 | 4 |
| FT5 | I am frustrated that I cannot work or contribute as much as I usually do | 0 | 1 | 2 | 3 | 4 |
| FT6 | I am satisfied with my current financial situation | 0 | 1 | 2 | 3 | 4 |
| FT7 | I am able to meet my monthly expenses | 0 | 1 | 2 | 3 | 4 |
| FT8 | I feel financially stressed | 0 | 1 | 2 | 3 | 4 |
| FT9 | I am concerned about keeping my job and income, including work at home | 0 | 1 | 2 | 3 | 4 |
| FT10 | My cancer or treatment has reduced my satisfaction with my present financial situation | 0 | 1 | 2 | 3 | 4 |
| FT11 | I feel in control of my financial situation | 0 | 1 | 2 | 3 | 4 |
| FT12 | My illness has been a financial hardship to my family and me | 0 | 1 | 2 | 3 | 4 |

English (Universal) 26 September 2017

Copyright 2014, FACIT and The University of Chicago

PROMIS® Item Bank v1.0 – Fatigue – Short Form 13a (FACIT-Fatigue)

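### Financial toxicity is scored once, with no baseline and no arm comparison, so the planned summaries cannot separate treatment effect from prior finances

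*Protocol*

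**What the plan says.** Section 1.0 of the Protocol asks whether an intermediate dose can be found that matches 24 Gy on disease control but "has shorter treatment course, lower clinical and financial toxicity, and less financial health care expenditure". Section 16.4.3 then defines the financial toxicity endpoint as "financial side effects induced by cancer treatment that will be assessed by a modified COST-FACIT questionnaire".

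The timing is stated consistently. Section 2.3 says: "Financial toxicity will be assessed at the end of radiation treatment". Section 7.2.3 repeats this with a window of one day either side, and Section 7.2.6 ties it to the last fraction in each arm. In the Section 4.0 test schedule, the row "Financial Toxicity Questionnaire" has a single mark, under End of Treatment, and its baseline cell is empty. FACIT-Fatigue, in the row above, is collected at baseline, end of treatment, Day 7 and 3 months.

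Section 16.6.2.5 scores items FT1 to FT11 on a 0 to 44 scale (higher is better) and says the "scores will be assessed at end of treatment and described separately for the two groups" using mean, SD, median and quartiles. It then states that the treatment groups will not be compared. The next paragraph of the same section plans a linear regression for the arm difference in health care expenditure.

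**The concern.** An effect induced by treatment is a contrast, either with the patient's own earlier state or with a comparable group treated differently. The plan collects no earlier state and declines the comparison that randomisation makes available. What remains is a level of financial well-being in each arm at one time point.

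That level includes finances that predate the trial. Of the scored items in Appendix II, FT6, FT7, FT8 and FT11 ask about the patient's general financial position, with no reference to illness or treatment.

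At stake is one part of the first question in Section 1.0. As written, the analysis would report two columns of summary statistics and no estimate of whether the shorter course reduces financial toxicity.

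**Working it through.** **Score range.** Eleven items scored 0 to 4 give 11 × 0 = 0 to 11 × 4 = 44, as Section 16.6.2.5 states.

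**What the summaries identify.** Let μ be the mean score the patients would have had before treatment (equal in expectation across arms under randomisation), and let δ₁ and δ₂ be the mean shifts by end of treatment in the experimental and control arms.

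- Expected experimental arm mean: μ + δ₁
- Expected control arm mean: μ + δ₂
- Expected difference: δ₁ − δ₂

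The plan reports the first two. Because μ is never measured, neither shift can be recovered. For illustration, arm means of 27 and 24 arise from μ = 28 with shifts of −1 and −4, and equally from μ = 25 with shifts of +2 and −1. The difference is 3 in both cases, and it is the one quantity that does not depend on μ.

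**Check that the end-of-treatment contrast is unbiased.** In 20,000 simulated trials with 51 per arm, assumed μ = 28, shifts of −1 and −4, a between-patient SD of 8 and added variation of SD 6, the arm means averaged 27.02 and 24.01. The difference averaged 3.01 against a true value of 3.

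**Precision of that contrast.** Inputs: 51 evaluable patients per arm (Section 16.1), assuming all return the form. The Protocol gives no SD for the COST score, so 8 to 12 points is assumed.

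Half-width of the 95% interval = 1.96 × SD × √(2/51) = 0.388 × SD.

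With the baseline score as covariate, at an assumed correlation r with the later score, this is multiplied by √(1 − r²): √(1 − 0.25) = 0.866 for r = 0.5, and √(1 − 0.64) = 0.600 for r = 0.8.

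| Assumed SD | No baseline | Baseline, r = 0.5 | Baseline, r = 0.8 |
| --- | --- | --- | --- |
| 8 | 3.11 | 2.69 | 1.86 |
| 10 | 3.88 | 3.36 | 2.33 |
| 12 | 4.66 | 4.03 | 2.79 |

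The reduction is 1 − 0.866 = 13% to 1 − 0.600 = 40%.

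**The case against.** The best defence is that this is a descriptive, exploratory item and the restraint is deliberate. The timing is the same wherever it is stated, so there is no contradiction in the schedule. Means and SDs are reported by arm, so a reader could work out the difference. The companion economic endpoint, expenditure, is compared. All of this is true and it limits the severity. It does not explain why one financial endpoint in Section 16.6.2.5 gets an estimated arm difference while the other is denied one, nor does it make a level at one time point match the definition in Section 16.4.3.

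Three stronger readings are tempting, and the documents do not support them.

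- *A reader might infer that the score measures prior finances and not treatment toxicity.* FT1 to FT4 and FT10 refer to illness, treatment or the cost of care. FT10 asks directly whether cancer or its treatment has lowered the patient's financial satisfaction. The added questions in Section 7.2.6 on travel, accommodation and lost work time address treatment burden itself. The score is a mixture.
- *A reader might infer that without a baseline no arm difference can be shown.* The randomised contrast is unbiased without one. A baseline adds precision and within-patient change.
- *A reader might infer that the recall period invalidates the timing*, since Appendix II asks patients to "indicate your response as it applies to the past 7 days". Using the 5 and 16 days in Section 4.0, recall from the last treatment day covers the whole shorter course plus about 2 days before it, but only 7/16 = 44% of the longer one. Most scored items, however, ask about a current state or worry, not events counted over a week. By the same measure, a 3-month form would cover no treatment days in either arm. Nor does the Protocol show that most costs arrive after the last fraction.

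**Conclusion.** The concern holds in a limited form. The endpoint is defined as an effect induced by treatment and supports part of the trial's first question, but the plan provides neither a baseline nor an arm comparison, so its summaries cannot separate that effect from prior finances. The remedy is largely analytic: data already scheduled would give an unbiased arm difference, with a 95% half-width of about 3.1 to 4.7 points if the SD is 8 to 12. The gain from a baseline, 13 to 40% of that half-width, rests wholly on an assumed correlation of 0.5 to 0.8.

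Severity is low. The endpoint is exploratory, and it enters neither the decision rule in Section 16.5.1.1 nor the sample size in Section 16.5.4.

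**What to change.** 1. In Section 16.6.2.5, replace the sentence ruling out a comparison with an estimated arm difference in the end-of-treatment COST score and a 95% confidence interval, labelled exploratory, in line with the regression already planned for expenditure. This needs no new data and covers patients already enrolled.

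2. In the Section 4.0 schedule, add the COST form at the baseline visit where FACIT-Fatigue is already collected. That visit precedes registration and so randomisation, which makes the score a proper covariate. Use it in the model where it is available. The added travel and work questions can stay at end of treatment only.

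3. A COST form at 3 months is optional. It would describe later financial well-being, but the point does not depend on it.

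If the sponsor prefers to keep the endpoint purely descriptive, Section 16.4.3 should instead call it financial well-being at end of treatment. The part of the Section 1.0 question on financial toxicity would then remain unanswered.

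The cost is one extra page at an existing visit and a protocol amendment. Patients already enrolled will have no baseline score, so the gain in precision will be partial.

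### The trial's rationale asks whether a lower dose reduces financial toxicity, but the plan rules out a between-arm estimate of the COST score

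*Protocol*

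**What the plan says.** The first of the two open questions in Section 1.0 (Background) asks whether a dose between 4 Gy and 24 Gy could control disease as well as 24 Gy with, among other gains, "lower clinical and financial toxicity, and less financial health care expenditure".

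Section 2.3 lists financial toxicity and health care expenditure next to each other as exploratory goals. For the first it says: "Financial toxicity will be assessed at the end of radiation treatment". Section 7.2.6 specifies a "questionnaire completed by the patient at the end of their ISRT (fraction 3 for experimental arm and fraction 12 for the SOC arm"), with added questions on travel, accommodation and lost work time. The test schedule in Section 4.0 has COST-FACIT at end of treatment only, with no baseline assessment.

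On analysis, Section 16.6.2.5 says: "The financial toxicity score will be summarized separately for the two treatment groups with the mean, standard deviation, median" and quartiles. The next sentence is "No comparison between treatment groups will be conducted". In the following paragraph, on expenditure, "a linear regression model will be used to estimate the difference in Financial health care expenditure between the two treatment arms".

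**The concern.** To ask whether financial toxicity is lower is to ask a comparative question, and the comparator is the randomised 24 Gy arm. The questionnaire is collected in both arms, and the burdens covered by its added items could plausibly depend on the number of visits. The plan nevertheless excludes the contrast and gives no reason. This is an explicit prohibition, not a detail left open for a statistical analysis plan: a later plan that compared the arms would depart from the protocol.

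What is at stake is modest. Two summaries will appear side by side and readers will compare them by eye. Without a planned interval, a chance gap can be over-read or a real one dismissed, and any comparison made later will be post hoc.

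**Working it through.** The protocol states no effect size, SD or power for financial toxicity, so there is no planned figure to reproduce. The check has four parts.

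**1. How comparable endpoints are treated**

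| Endpoint | Status | Between-arm analysis |
|---|---|---|
| COST score | Exploratory (2.3, 16.4.3) | Ruled out (16.6.2.5) |
| Health care expenditure | Exploratory (2.3, 16.4.4) | Direct comparison (7.2.7); linear regression (16.6.2.5) |
| FACIT-Fatigue | Secondary (2.2, 16.3) | Mixed model, arm-by-time interaction with 95% interval (16.6.2.4) |

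The exploratory label alone does not explain the exclusion, because expenditure carries the same label and is compared. Nor does the fact that the data are patient-reported, because FACIT-Fatigue is compared.

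**2. What the planned output would still allow**

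Each arm's mean and SD will be reported. If the numbers of completers n1 and n0 are also reported, a reader can compute

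difference = mean1 − mean0, with 95% interval difference ± 1.96 × √(SD1²/n1 + SD0²/n0).

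So an unadjusted contrast can be recovered. What is missing is the trial's own pre-specified estimate.

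**3. Precision if the estimate were planned**

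Inputs:
- 51 evaluable patients per arm (Sections 16.1 and 16.5.4).
- Score range 0-44 (Section 16.6.2.5), which checks as 11 items × 4 = 44.
- The SD is not in the protocol. SDs of 8, 10 and 12 points are assumptions that show a range.
- Completion is not projected either. 51 per arm is full completion; 45 and 40 are assumed for illustration.

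Half-width of the 95% interval, with equal SDs and no covariates = 1.96 × SD × √(2/n). At n = 51: 1.96 × √(2/51) = 0.388 SD.

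| Completers per arm | In SD units | SD 8 | SD 10 | SD 12 |
|---|---|---|---|---|
| 51 | 0.39 | 3.1 | 3.9 | 4.7 |
| 45 | 0.41 | 3.3 | 4.1 | 5.0 |
| 40 | 0.44 | 3.5 | 4.4 | 5.3 |

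**4. When the score is measured**

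Section 4.0 gives treatment lengths of about 5 days for 3 fractions and about 16 days for 12 fractions. The questionnaire in Appendix II asks about the past 7 days. At the end of treatment the recall period therefore starts about 7 − 5 = 2 days before treatment in the 3-fraction group, and about 16 − 7 = 9 days into treatment in the 24 Gy arm. With no baseline score, the contrast rests on randomisation, with the stratification factors as the available design covariates.

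**The case against.** The strongest defence is that no stated objective is contradicted. The comparative wording stands in the background. The purpose statement that closes Section 1.0 does not mention financial toxicity, the goal in Section 2.3 is only to assess it, and the decision rules in Section 16.5.1 do not use it. The protocol also separates the two financial outcomes consistently: Section 7.2.7 promises a comparison for costs and Section 7.2.6 promises none for the questionnaire. The unequal timing and missing baseline make a difference harder to interpret. All of this is fair. It keeps the point minor and would make a descriptive analysis defensible if the protocol gave that reason, which it does not.

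The timing argument limits interpretation but does not invalidate the contrast. Randomised groups compared at the end of their assigned course give a valid end-of-treatment comparison, provided it is described as such. The same limitation applies to the two arm-wise summaries that the plan will publish anyway.

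A reader might go further and infer that the trial cannot answer its question on financial toxicity, or that it makes no financial comparison at all. The documents support neither. The arm-wise means and SDs, with completer counts, are enough to derive a difference and interval. The bar applies to the COST score, while expenditure, the other financial part of the question, is compared. It would also be wrong to judge this endpoint against the two-sided 0.10 level, which the protocol sets for the primary endpoint only.

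**Conclusion.** The mismatch is real and small. The rationale includes a comparative question about financial toxicity and the data come from both randomised arms, but Section 16.6.2.5 excludes the comparison without a reason while making one for expenditure. The consequence is the loss of a pre-specified estimate with its uncertainty, not the loss of the information.

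An estimate would have useful though limited precision: a 95% half-width of about 0.39 SD with full completion. The values in points rest on an assumed SD of 8 to 12, equal SDs in the two arms and 51 completers per arm; fewer completers widen the interval. The primary analysis and the decision rules are unaffected.

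**What to change.** In Section 16.6.2.5, replace the sentence that excludes a comparison with:

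*The between-arm difference in mean COST score at end of treatment will be estimated by linear regression on treatment arm, adjusted for the stratification factors, with a 95% confidence interval. This is exploratory, without a formal test, and not part of the decision rule.*

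The type of model is the one already named for expenditure. Adjustment for the stratification factors in Section 5.0 is an addition, since the expenditure text names no covariates.

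Also report the number of completed questionnaires per arm. State that there is no baseline COST score and that the assessment falls about 5 versus 16 days after the start of treatment with a 7-day recall, so the estimate is an end-of-treatment contrast.

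The cost is a few sentences and one regression on data already collected, with no extra patients, visits or forms. The downside is one more exploratory estimate, labelled as such. If the sponsor prefers to keep the endpoint descriptive, the protocol should give the reason and the background question should be worded to match.
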